### Outcome measures

#### Structured Interview Guide for the Hamilton Rating Scale for Depression—Seasonal Affective Disorder Version (SIGH-SAD)

The SIGH-SAD [34] includes the 21-item Structured Interview Guide for the Hamilton Rating Scale for Depression (HAM-D) and a supplementary 8-item subscale to assess atypical depressive symptoms associated with SAD. A trained rater, blind to the treatment condition, administers the SIGH-SAD at pre-treatment, treatment weeks 1–5, post-treatment, summer follow-up, next winter follow-up, and second winter follow-up. A second blinded rater subsequently rates audiotapes of the live SIGH-SADs to assess inter-rater reliability.

The primary outcome, depression recurrence status in the next winter, is defined according to the following SIGH-SAD criteria [35]: total SIGH-SAD score ≥ 20 + HAM-D score ≥ 10 + atypical score ≥ 5. The same criteria are used to define SAD episode onset (i.e., study inclusion criterion b) and depression recurrence status at follow-ups. Continuous depression scores and remission status on the SIGH-SAD represent secondary outcome measures. One or both of the following SIGH-SAD criteria are used to classify a full remission at post-treatment [36]: pre- to post-treatment reduction in total SIGH-SAD score ≥ 50% + HAM-D score ≤ 7 + atypical score < 7 OR HAM-D score ≤ 2 + atypical score ≤ 10. These remission criteria are also used to define remission status at the summer follow-up and annual winter follow-ups, except that the respective follow-up SIGH-SAD score, as opposed to the post-treatment score, is contrasted to baseline status.

#### The Longitudinal Interval Follow-up Evaluation (LIFE)

The LIFE [36] is a semi-structured interview that assesses the longitudinal course of psychiatric disorders, including remissions and recurrences. This study uses the psychopathology section of the LIFE, which provides weekly depression status ratings on a continuous symptom scale ranging from 1 (usual self; no residual depressive symptoms) to 6 (definite DSM-IV-TR Major Depressive Episode criteria and extreme impairment), to assess depression in the following three interim periods: between post-treatment and the subsequent summer follow-up, between summer follow-up and the next winter follow-up, and between the next winter follow-up and the second winter follow-up. Any 2-week or longer period of depression ratings in the range of 5 (the threshold for meeting DSM-IV-TR Major Depressive Episode criteria) or 6 will be used as a secondary outcome of depression recurrences that occur between assessments. The LIFE was used in this way in a 2-year follow-up of depressed patients treated with cognitive therapy or antidepressant medications to capture relapse and recurrence [16,37]. A trained and blinded clinical graduate student rater administers the LIFE live, and a second blinded clinical graduate student rates an audiotape of the LIFE to assess reliability for detecting recurrences in these interim periods.

### Beck Depression Inventory—Second Edition (BDI-II)

The BDI-II [38] is a 21-item measure of depressive symptom severity that constitutes a secondary outcome measure, administered at pre- and post-treatment, summer, next winter, and the second winter. The BDI-II has demonstrated good test-retest reliability and convergent validity [38]. Consistent with the pilot trials [11,21,22], BDI-II ≤ 8 is a secondary measure of remission status.

### Protocol for training clinical raters and ensuring accuracy of scores

To train SIGH-SAD raters, each year of recruitment, the PI leads several sessions with the study team to discuss each of the 29 SIGH-SAD items in detail and the nuances of scoring them. Subsequently, each year, the raters practiced rating at least three audiotapes of SIGH-SADs from past studies and discussed their ratings in a group session lead by the PI. Trainees were required to observe a veteran rater perform a live SIGH-SAD in the study, record their ratings, and discuss them with the interviewer after the session. To become an independent rater, a trainee had to perform a mock SIGH-SAD interview on the PI (role-playing a patient) with good flow and proficiency and obtain item ratings that corresponded well to the PI’s judgments.

The following protocol was developed to increase the accuracy of SIGH-SAD scores. The project statistician identifies any SIGH-SAD administration with a 5-point or greater discrepancy in total score (minus items H16 and H17, which require a direct observation of the patient) between the original and second rater. In these cases reaching the threshold for an unacceptable split between raters, two additional blinded raters are selected from our team to re-rate those particular interviews. The statistician then examines ratings from all four raters of each tape to identify SIGH-SAD items where the original rater disagreed with two or three of the other three raters. Subsequently, the two new raters discuss those particular SIGH-SAD items and try to reach a consensus on the most accurate score for them. If a consensus cannot be reached, the PI is consulted about what was said on the tape (keeping her blind to subject identity, and, therefore, group assignment) to make a final decision about the most accurate score for that item. Any corrected SIGH-SAD scores will be used in the primary and secondary analyses. However, inter-rater reliability statistics will still reflect agreement between the original (uncorrected) rater and the second rater.

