#### Light therapy (LT)

Participants randomized to LT attend an instructional session, standardized using a pre-generated script of points to cover: the LT treatment rationale, demonstration of assembly and positioning of the light box, prescription for daily use (i.e., timing and duration), possible side effects, and explanation of the daily LT self-monitoring diary and the side effects questionnaire. These sessions are audiotaped to assess treatment integrity. The PI conducts the sessions because the PI and the project coordinator are the only un-blinded personnel who work directly with participants, and the PI is qualified to answer any questions that arise.

LT participants use the SunRay (SunBox Company, Gaithersburg, MD), a standard LT unit (23 × 15½ × 3¼ inches) with an ultraviolet shield that emits 10,000 lux of white fluorescent light to the retina when the user is within 18 inches. Participants keep daily LT compliance diaries to record the timing and duration of LT. For each of the 6 treatment weeks, LT participants complete an LT side effects questionnaire to assess the presence and severity of any side effects attributed to LT (e.g., headache, eyestrain, feeling “wired) and self-reported times for onset of sleepiness, onset/offset of actual sleep, and desired times for onset/offset of sleep over the previous week. Although individuals typically respond within 4 weeks of initiating LT or not at all [7], our protocol is maintained and monitored for a full 6 weeks to match the duration of the CBT condition. To circumvent ethical concerns regarding discontinuation of a potentially beneficial treatment during the winter when relapse is likely [1], participants can choose to continue using the light box through April and are asked to return it in May. However, in an effort to reduce access to a suitable LT unit as a potential confound, LT participants who wish to use LT in the next fall/winter season are offered access to our light boxes if they agree to consult a provider for side effects management if needed. Continuing ongoing clinical management of LT under our supervision the next winter would create a potentially important confound as we do not offer to provide continued CBT or regular contact for CBT-treated participants. The chosen strategy strikes a balance between research design issues and ethical concerns related to patient safety.

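### Re-rating of SIGH-SAD interviews is triggered only by a 5-point gap in total score, so raters can disagree on the primary recurrence status without any review

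*Protocol article*

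**What the plan says.** The article's section on outcome measures (SIGH-SAD) defines next-winter recurrence, the primary outcome, as "total SIGH-SAD score ≥ 20 + HAM-D score ≥ 10 + atypical score ≥ 5". All three conditions must be met, and two of them concern subscales. A blinded rater conducts the interview, and a second blinded rater scores the audiotape.

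The section on training raters and ensuring accurate scores fixes the correction procedure:

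- **Trigger:** "any SIGH-SAD administration with a 5-point or greater discrepancy in total score", computed "minus items H16 and H17, which require a direct observation of the patient". No trigger is named for disagreement on recurrence status or on either subscale.
- **Re-rating:** "two additional blinded raters are selected from our team to re-rate those particular interviews".
- **Resolution:** for items on which the original rater is out of line with at least two of the other three, "the two new raters discuss those particular SIGH-SAD items and try to reach a consensus".
- **Last resort:** "If a consensus cannot be reached, the PI is consulted about what was said on the tape". The same sentence says that the PI is kept unaware of who the participant is, and hence of the group.

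Corrected scores go into the primary and secondary analyses. Where the trigger is not met, the procedure makes no correction, so the original rating stands.

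**The concern.** The trigger measures disagreement on a different scale from the primary endpoint. A 5-point gap in total suits the continuous SIGH-SAD score, which is a secondary outcome. The primary outcome changes at a boundary. A 1-point difference at the boundary matters for it, while a 6-point difference far from any boundary does not.

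The rule can therefore spend re-rating effort on interviews whose primary status nobody disputes, and pass over interviews where two blinded raters have already given opposite answers. Some of the disputed statuses will be wrong. Because the raters are blinded, such errors should be unrelated to arm, and they would pull the observed recurrence difference towards zero.

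**Working it through.** **1. Can the status flip without a trigger?** Apply the two rules to pairs of ratings, holding H16 and H17 the same for both raters.

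| Original rater | Second rater | Gap in total | Status | Re-rated? |
|---|---|---|---|---|
| HAM-D 10, atypical 10, total 20 | HAM-D 9, atypical 10, total 19 | 1 | yes / no | no |
| HAM-D 16, atypical 4, total 20 | HAM-D 15, atypical 5, total 20 | 0 | no / yes | no |

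The gap follows from the text alone. No assumption about rater error is needed.

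**2. The plan's own sample size.** The inputs from the sample-size section are 52% (LT), 29% (CBT), two-sided alpha 0.05, 80% power, and a mean proportion of 0.405.

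- Uncorrected: n = [1.96·√(2·0.405·0.595) + 0.8416·√(0.52·0.48 + 0.29·0.71)]² / 0.23² = (1.3607 + 0.5680)² / 0.0529 = 70.3, so 71 per group.
- With continuity correction: (70.3/4)·[1 + √(1 + 4/(70.3·0.23))]² = 78.8, so 79 per group.

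The stated 80 per group is reproduced with the correction. With the uncorrected test, power at 80 per group is 0.849.

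**3. How often would it happen?** The article gives no reliability figure, so this step rests on assumptions. Two simulations with different set-ups were run, 400,000 interviews per setting.

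- Set-up A: HAM-D mean 10, SD 7.5; atypical mean 7, SD 5.5; correlation 0.55; independent rater error with SD 1.2, 1.5 or 2.0 on each subscale.
- Set-up B: the article's next-winter means (14.3 and 19.5) and SD 11.5; 60/40 split between HAM-D and atypical; subscale correlation 0.6; figures averaged over the arms.

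| Set-up | Assumed reliability of total | Share of status disagreements with gap under 5 | Unreviewed, of all interviews | Per 160 |
|---|---|---|---|---|
| A | about 0.97 | 83% | 5.8% | 9.2 |
| A | between | 70% | 6.0% | 9.6 |
| A | about 0.94 | 52% | 5.9% | 9.4 |
| B | 0.95 | 57% | (5.5 + 6.3)/2 = 5.9% | 9.4 |
| B | 0.90 | 38% | (5.0 + 5.9)/2 = 5.45% | 8.7 |
| B | 0.85 | 29% | (4.7 + 5.6)/2 = 5.15% | 8.2 |

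The share depends strongly on the assumed error, but the count hardly moves. In set-up A, about three quarters of the interviews that the 5-point rule does flag involve no status disagreement.

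**4. From disagreement to error.** In set-up A the original rater is wrong in about 50% of the unreviewed disagreements, or about 4.7 per 160. Re-raters also err. With their consensus modelled as the mean of two new ratings, the added trigger removes a net of about 2.5 misclassifications per 160, or 2.5/160 = 1.6%.

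**5. Effect on the comparison.** With error rate e in both directions, an observed proportion is p(1 − e) + (1 − p)e, so the difference becomes (1 − 2e)·23 points.

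- e = 1.6%: loss of 2·0.016·23 = 0.7 points.
- e = 2%: difference 22.1 points, power 0.817 (uncorrected test, against 0.849 with no error).
- e = 5%: difference 20.7 points, power 0.762. This exceeds what step 4 supports and is shown for scale only.

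**The case against.** **The total-score rule has a purpose.** It applies to every SIGH-SAD administration, and continuous scores are secondary outcomes. That stands. It is a reason to keep the 5-point trigger, but not a reason to leave the primary status unchecked.

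**Many flips are caught.** A reader might infer that disagreements on recurrence status generally go uncorrected. They do not: those with a gap of 5 or more are re-rated, which is 17–48% of them in set-up A and 43–71% in set-up B.

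**Disagreements are not errors.** Reading 8 to 10 disputed interviews as 8 to 10 wrong outcomes would overstate the loss by a factor of three or more. The base of 160 is also an upper limit, since missing next-winter scores are imputed and those participants have no tape. Both points stand.

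**The PI as final arbiter.** The light therapy section says that "the PI and the project coordinator are the only un-blinded personnel who work directly with participants", and the PI runs the LT instructional sessions and is one of three CBT group therapists. A reader might conclude that an unblinded person settles primary outcome scores. The article does not support this. The PI is reached only after two further blinded raters fail to agree, and is masked to identity and group at that step. What remains is a residual risk that someone who treats participants recognises a case from the tape content. The article neither shows that this happens nor gives a way to size it.

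**The tape rater has no complete score.** H16 and H17 cannot be rated from tape, so recurrence status by the second rater is undefined without a rule for them. That is right, and the fix has to supply one.

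**Conclusion.** The concern holds as a mismatch between the trigger and the primary endpoint. That part is certain from the text. Its size is modest and rests on assumed rater error: about 5–6% of completed next-winter interviews with an unreviewed status disagreement, and a net 2 to 3 avoidable misclassifications per 160. The expected effect is a dilution of under one percentage point in the recurrence difference, with no bias towards either arm so long as raters stay blinded.

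It should not be read as an error in the stated power. The calculation reproduces, and the 52% and 29% come from pilot ratings that carried rater error themselves. This is a cheap improvement to the scoring of the primary outcome and does not put the trial's conclusion in doubt.

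**What to change.** For the next-winter and second-winter interviews, keep the 5-point trigger and add a second one:

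- Re-rate any interview in which the original and second rater differ on recurrence status under the three criteria.
- For this comparison, use the original rater's H16 and H17 values for both raters.
- Resolve the interview by the existing route of two further blinded raters and item consensus, with everyone involved blind to arm.

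The cost is up to about 10 more tapes per 160 interviews, using recordings and raters that the trial already has. To deal with the residual recognition risk, it would help to state in one sentence how masking is kept when the PI is consulted.

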### Data analysis plan

The primary analysis is an intent-to-treat (ITT) analysis based on multiple imputation (MI) of missing next winter SIGH-SAD scores [39-41]. Imputed scores will be used to classify depression recurrence status for individuals who dropped out during the treatment phase, were withdrawn from protocol, or were subsequently lost to follow-up. Imputed values will be generated from multivariate normal models derived from subjects with next winter follow-up data, using baseline and post-treatment SIGH-SAD, HAM-D, and atypical scores, demographic variables (e.g., gender, race, age), and other baseline patient characteristics (e.g., presence of a comorbid axis I disorder, antidepressant medication status) as potential predictors. Separate models will be developed for the CBT and LT groups rather than including treatment group in the model as a predictor, because in the pilot study, baseline SIGH-SAD scores were negatively correlated with next winter scores in CBT and were positively correlated with next winter scores in LT. Outcomes for subjects with missing next winter data will be predicted from the models based on available data and a random component reflecting the residual distribution for the dependent variable. Ten data sets with different imputed values will be generated, and a dichotomous variable indicating recurrence status will be computed for each subject based on SIGH-SAD criteria. The difference between the CBT and LT groups in the proportions of subjects with a recurrence the next winter will be estimated for each of the ten data sets and the estimates will be combined using the inference methods for MI described by Little and Rubin [42]. SAS PROC MI and PROC MIANALYZE will be used to carry out the imputation and analysis. Sensitivity analysis will be conducted to determine the robustness of the results under alternative MI models and imputation methods, including best and worst case scenarios for each treatment.

The above analysis will be repeated using the following alternate recurrence definitions as secondary outcomes: (1) meeting SIGH-SAD recurrence criteria at the prospective next winter follow-up OR depression recurrence defined as any major depressive episode as assessed by the LIFE OR fulfilling DSM-IV-TR major depression criteria in the interim between summer and next winter as assessed by the October and December tracking telephone calls, (2) a recurrence on the next winter SIGH-SAD OR depression recurrence status as assessed by considering any new treatment reported in the interim between treatment endpoint and next winter follow-up (except for ongoing LT for LT participants and using CBT skills on their own without a therapist for CBT participants) as prima facie evidence of recurrence, and (3) the most encompassing and conservative definition of recurrence that defines a recurrence as fulfilling criteria (1) OR (2) above.

Secondary analyses will examine how potential modifiers influence the effects of CBT and LT on the primary outcome of next winter recurrence on the SIGH-SAD. Potential modifiers will include: (1) demographic variables such as sex, age, and race (White vs. minority); (2) baseline characteristics such as pre-treatment depression scores, axis I comorbidity, and baseline antidepressant medication status; and (3) complete or incomplete summer remission status in the interim, as ascertained by the SIGH-SAD at the summer follow-up. This will be done using logistic and linear regression analyses for dichotomous and continuous outcomes, respectively, and including the modifiers as well as their interactions with treatment in the models. Although the models are essentially the same as those fitted to the complete data for the purpose of imputation, for this analysis they will be fitted to the imputed data sets, and the Rao-Blackwell estimates of the effects of the modifiers will be obtained [43].

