### Phone tracking of recurrences and retreatment

A blinded clinical graduate student telephones each participant twice in the interim between summer follow-up and the in-person next winter follow-up: once in October and once in December. The purpose of these brief phone contacts is to track any recurrences and any new treatments initiated. To track recurrences, DSM-IV-TR criteria for a major depressive episode on the SCID-CV are assessed for the interval between the present and last contact (i.e., formal assessment or phone call). To track retreatment, the caller asks, “Have you started any new treatments since (date of last contact) such as LT, talk therapy, or medications?” If the participant answers affirmatively, he or she is queried for specific details.

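### The listed predictors for the primary imputation stop at post-treatment, so interim depression data that the trial already collects do not inform missing next-winter scores

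*Protocol article*

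**What the plan says.** Under Data analysis plan, the Protocol article states: "The primary analysis is an intent-to-treat (ITT) analysis based on multiple imputation (MI) of missing next winter SIGH-SAD scores". Scores are imputed for "individuals who dropped out during the treatment phase, were withdrawn from protocol, or were subsequently lost to follow-up". The potential predictors are given as "using baseline and post-treatment SIGH-SAD, HAM-D, and atypical scores, demographic variables (e.g., gender, race, age), and other baseline patient characteristics". The models are fitted by arm: "Separate models will be developed for the CBT and LT groups rather than including treatment group in the model as a predictor". Sensitivity analyses under other imputation models and under best and worst cases are promised, but no interim variable is named for them.

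The trial records much between the end of treatment and the next winter. A blinded rater gives the SIGH-SAD in the summer, and the BDI-II is repeated then. The LIFE covers post-treatment to summer and summer to next winter. Telephone contacts take place "once in October and once in December" and ask about major depressive episodes and new treatments. All randomized participants are invited to the follow-up visits.

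These interim data appear in the analysis in two places only. One is the secondary recurrence definitions: "The above analysis will be repeated using the following alternate recurrence definitions as secondary outcomes". The other is the modifier analysis, where summer remission status is one of the modifiers. The plan says there that the modifier models and the imputation models are in essence the same.

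**The concern.** The primary outcome is measured in January or February of the following winter, many months after the last predictor on the list. Someone lost to follow-up late can have a summer score and two telephone assessments but no winter score. For that person the listed model uses nothing recorded after treatment ended, although the interim data lie closest in time to the outcome and may be related to dropout. Missing at random is then assumed conditional on less information than the trial holds. If dropout depends on interim status in one arm more than in the other, the estimated difference in recurrence moves.

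There is also a conflict within the section. Either summer status is in the imputation models, and the predictor list is incomplete, or it is not, and the remark about the modifier models is wrong. If it is not, testing summer remission by treatment on data imputed without summer remission pulls that interaction toward zero for the imputed cases.

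**Working it through.** **1. The plan's own figure.** Sample size section: 52% (LT) vs 29% (CBT), two-sided alpha 0.05, power 80%, stated as 80 per group.
- Mean proportion = (0.52 + 0.29)/2 = 0.405.
- n = [1.96·√(2·0.405·0.595) + 0.8416·√(0.52·0.48 + 0.29·0.71)]² / 0.23² = 70.3, so 71 per arm.
- With continuity correction: (70.3/4)·[1 + √(1 + 4/(70.3·0.23))]² = 78.8, so 79 per arm.

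The stated 80 is reproduced. No stated number is disputed here.

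**2. What could be known when the winter score is missing.**

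| Data | Timing | Obtainable if the winter visit is missed? | On the predictor list? |
|---|---|---|---|
| SIGH-SAD and subscales | baseline, post-treatment | yes | yes |
| SIGH-SAD and subscales, BDI-II | summer | yes | no |
| LIFE, post-treatment to summer | presumably at the summer visit | yes | no |
| Major depression and new treatment by telephone | October, December | yes | no |
| LIFE, summer to next winter | presumably at the winter visit | probably not | no |

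**3. How much may be missing.** The article gives no expected fraction for this trial. The pilot allows a rough value. If d is the missing fraction and p the recurrence rate in those observed, the worst-case rate is d + (1 − d)p, so d = (worst case − p)/(1 − p). Taking the pilot's imputed rates as a stand-in for p (an assumption):
- LT: (0.52 − 0.367)/(1 − 0.367) = 24%.
- CBT: (0.29 − 0.07)/(1 − 0.07) = 24%.

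As a cross-check, the pilot follow-up reports 17 people with imputed outcomes. The two pilot studies randomized at most 26 + 61 = 87, so at least 17/87 = 19.5% were missing.

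**4. Large-sample effect on the difference.** Normal winter scores were cut to give 52% and 29% recurrence, with 400,000 per arm and arm-specific normal imputation. Assumptions not in the documents: baseline/post-treatment correlation with the winter score 0.3; interim correlation 0.4 to 0.7; missing 10 to 30%; log-odds slope of missingness on interim status 0 or ±1 per SD. Every missing participant has interim data. The true difference is 0.23.

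| Missingness depends on interim status | Listed predictors, 20% missing, correlation 0.6 | Listed predictors, all settings |
|---|---|---|
| in neither arm | 0.230 | about 0.23 |
| equally in both arms | 0.229 | about 0.23 |
| in LT only | 0.193 | 0.17 to 0.22 |
| in CBT only | 0.264 | 0.24 to 0.29 |
| in opposite directions | 0.169 or 0.299 | 0.12 to 0.36 |

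With interim status added to the model, the estimate stays at about 0.23 in every setting.

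**5. At trial size.** 80 per arm, 20% missing, interim correlation 0.6, ten imputations, Rubin's rules, 1,500 runs:
- Missingness unrelated to interim status: standard error 0.083 (listed) vs 0.082 (with interim); power 79% vs 80%.
- Related in LT only: power 64% vs 79%.
- Related in CBT only: 89% vs 79%. The higher figure reflects an overstated effect and is not a gain.

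**6. Dilution.** Treatment-phase dropouts may have no interim data. With 24% missing, half of them without interim data, and interim correlation 0.6, the listed model gives 0.205 to 0.216 (LT only) or 0.243 to 0.253 (CBT only). With a shared mechanism at 24% missing it gives 0.227 to 0.228.

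**7. Coherence of imputed scores.** Recurrence requires "total SIGH-SAD score ≥ 20 + HAM-D score ≥ 10 + atypical score ≥ 5". The total is the 21-item HAM-D plus the 8 atypical items, so imputed values should respect that sum.

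**The case against.** The list is introduced as potential predictors, with examples, so it need not be exhaustive. The remark about the modifier models could mean that summer status does enter the imputation. Sensitivity analyses under alternative imputation models are promised. These points stand in part. They make the plan ambiguous, but no interim variable is named for the imputation anywhere, and sensitivity analyses do not change the primary estimate. The two statements conflict; neither cures the other.

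Several stronger readings are tempting and are not supported:
- That a person with a December episode and no winter visit is imputed as though nothing were known. Baseline and post-treatment data are still used, and a December episode predicts the January or February SIGH-SAD status without being that outcome.
- That the whole weekly LIFE record is wasted. The summer-to-winter part would probably be missing together with the winter visit.
- That the secondary definitions must under-count recurrence. Their components are joined by OR, so an observed episode or new treatment already counts. Only unobserved components are at issue, and the article does not say how these are handled.
- That bias in one arm's recurrence rate carries over to the result. The analysis estimates a difference, and the pilot arithmetic gives the same 24% in both arms, which is no evidence of differential dropout.
- That power would rise noticeably. A calculation with 24% missing gives 76% when predictors explain nothing and 79 to 82% when they explain 30 to 50%, but the planned model already has predictors. Like for like the change is about 79% to 80%.

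**Conclusion.** The point holds as a worthwhile improvement to the primary analysis, together with an inconsistency to resolve. The predictor list is stated in the article, so this is not a detail left to an unseen analysis plan. The gain is protection against bias, not precision.

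Under the assumed 20% missing, interim correlation 0.6 and a one-arm mechanism, a true difference of 0.23 is estimated at about 0.19 or 0.26. The shift is smaller if many missing participants have no interim data, and near zero if both arms share the mechanism. Its direction cannot be predicted from the documents, which also do not say how many participants will have interim data but no winter score. A reader might infer that the planned primary result will be biased; the documents show only that it could be, and that the means to reduce the risk are already being collected.

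**What to change.** - Add a few interim summaries to the arm-specific primary imputation models: summer HAM-D and atypical scores, October and December major-depression status, and interim new treatment. Post-treatment-to-summer LIFE status or summer BDI-II are optional.
- Impute HAM-D and atypical scores jointly and derive the total as their sum, so that the three-part recurrence rule is applied to coherent values.
- Impute the unobserved components of recurrence definitions (1) to (3) in the same run, and count any observed interim episode or new treatment as recurrence under the definition that includes it.
- Reconcile the predictor list with the remark that the modifier models match the imputation models.
- Keep the currently listed model as a sensitivity analysis.

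The cost is wording and programming, with no new data. The drawback is a larger imputation model with about 80 participants per arm, some of them without a winter score, so the added variables should be few.
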